## 6.2 Clinical Acumen Model

Although psychiatric treatment is generally not currently available in HIV clinics (nor general primary care clinics) in Uganda, clinics that are looking to increase their provision of depression treatment are likely to follow the model used in many other parts of the world, which is to train primary care providers to identify and treat depression. Similarly, the clinical acumen model of depression care relies on the discretion of primary care providers who receive depression care training to provide depression diagnosis and treatment as deemed warranted. To facilitate this

process, like the protocolized model, the clinical acumen arm also includes routine screening of all adult clients and monthly on-site supervision from study psychiatrists. However, this model relies on the clinical judgment of the primary care provider to decide whether to further evaluate and treat patients who screen positive for possible depression, as opposed to a structured protocol (see Table 1 for an outline of the model and how it compares to the protocolized model). Another difference between the models is that depression care is managed entirely by nurses (with oversight from the clinical/medical officer in charge) in the protocolized model, whereas in the clinical acumen model all primary care providers (who are comprised of nurses and clinical/medical officers) are expected to provide depression care.

### 6.3 Training, Supervision and Monitoring

Training and ongoing supervision are critical for ensuring quality of care and fidelity to the depression care models, and to provide technical and emotional support to the providers. With management of antidepressant treatment being new to the clinic staff, the supervision is particularly important and will help to increase the confidence of the providers in their ability to provide high quality care. Supervision is also an opportunity for the providers to refresh and upgrade their new skills in an ongoing forum that reinforces the value of the investment they have made in the training and the integration of depression care into their HIV care practice. Furthermore, working with patients who are depressed can be stressful and emotionally draining, so the support from supervision can help prevent burnout and job turnover. The training and supervision provided to the clinic staff in both arms of the study is very similar; the only differences are that the providers in the clinical acumen arm will not be trained to follow the parameters of a structured protocol when further assessing patients who have screened positive for possible depression. The manual used to train the providers, and which was provided to each provider to take back to their clinic for reference, is included as an attachment.

**Start-up Training:** Training will start with the study's lead investigators and psychiatrists conducting an intensive one-day training workshop with the clinic staff (expert clients/VHTs, nurses, clinical/medical officers) to train them on the structure and goals of the study, and each component of the treatment model. One workshop will be held for the clinics in the protocolized arm, and a separate workshop for those in the clinical acumen arm. All nurses and clinical/medical officers at each site will be trained so that duties can be evenly spread, to build overall capacity for depression care, and to mitigate against the effects of occasional staff transfers. Training will consist of didactic instruction, interactive role-playing, and small breakout group discussions. Following the workshop, tools to facilitate implementation of the model (laminated copies of the PHQ-2 for the triage station, and PHQ-9/MINI for each nurse/prescribing provider, Depression Treatment Registry, psychoeducation posters and flipcharts) will be delivered to each site, and supervising psychiatrists will be on-site one day a week for 4-6 weeks (until both the supervisor and nurse are comfortable with the nurse's competency in implementing the protocol) to provide training and mentorship (e.g., sitting in on and co-conducting assessments), after which ongoing on-site supervision will become monthly.

**Ongoing Supervision:** Supervision will be conducted in one-on-one sessions between the site supervisor and each nurse (protocolized arm) and primary care provider (clinical acumen arm), as well as group meetings with all clinic staff involved with implementation of depression care at the site. Furthermore, the supervisor will be available 24/7 for emergency or suicide crisis consultations. During individual supervision, the providers will present new treatment cases since last supervision and problematic or nonresponding cases, allowing the supervisor to discuss the patient's presenting symptoms and the treatment plan for the patient, including side effect management and dose change recommendations. Clinical notes from the Depression

Treatment Registry will be used in the case reviews. Goals of treatment for the individual patient will be discussed and recorded for review at subsequent supervision sessions. The group meetings will provide an opportunity for the clinic staff to work as a team to trouble-shoot any challenges that arise, share experiences and provide peer support to each other in managing depressed patients, which can be taxing emotionally as well as fulfilling.

**Monitoring Fidelity:** Ongoing supervision and review of cases is our primary mechanism for monitoring the fidelity of the implementation of the treatment models. At each monthly supervision, supervisors review the charts of all patients prescribed antidepressants within the past month, as well as 10 randomly selected charts of patients receiving ongoing antidepressant treatment monitoring. The charts will be reviewed for whether diagnosis, symptoms and side effect assessment, and dosing were appropriately performed, and if the patient returned for follow-up visits. Results will be aggregated and monitored on a monthly basis, as well as used to inform the target areas for supervision.

## 7.0 DATA SOURCES

To evaluate the two task-shifting models, we will compare the implementation, effectiveness, and cost-effectiveness of these models over a 24-month period. Using the RE-AIM framework, we will evaluate the *reach* of depression screening and treatment, *adoption* of depression treatment knowledge and intervention by providers, *quality of implementation* (fidelity to depression care model), and *effectiveness* of depression treatment on patient outcomes. As outlined in Table 2, these implementation domains and corresponding outcomes will be assessed from data triangulated from these data sources: (1) data abstracted from data collection mechanisms integrated into routine care; (2) monthly logs summarizing chart abstracted data completed by the supervising psychiatrists; (3) survey data from a longitudinal cohort of randomly selected patients at each site who screen positive for potential depression (PHQ-9 > 2); and (4) survey data from longitudinal cohort of providers involved in provision of depression care at each site. Survey data from the patient cohort will also be used to assess how change in depression is related to key economic and public health outcomes. These data sources are described in more detail below.

**Routine data abstraction:** We will assess the implementation of screening (% of adults screened; % screened who screen positive) by abstracting data from the Triage Book, which the triage station at each site uses to list the clients who attend each day of the clinic, their vital signs, and PHQ-2 score. PHQ-9 and MINI administration data will be recorded in the patient's clinic chart. Depression Treatment Registry books will be installed at each site for providers to document clients who have started antidepressant therapy and their depression diagnosis, and records of each follow-up visit that include PHQ-9 score, presence of side effects and medication and dose prescribed.

**Supervision log data:** From the chart reviews that the supervisors conduct each month at each site, monthly aggregate scores are recorded for newly prescribed patients (number with correct diagnosis, correct prescribed antidepressant, and correct prescribed dosage) and patients in ongoing treatment (number correctly assessed for depressive symptoms and side effects; number correctly dosed; and number who returned for scheduled follow-up visit in past month).

**Longitudinal client cohort:** The client research participants will be assessed at baseline and months 6 and 12. The surveys will be administered by the research coordinator using computer assisted personal interview technology, and will include the PHQ-9 (to independently assess the presence of depression) as well as measures of demographic and background characteristics,

work activity, clinical appointment and ART adherence, quality of life, sexual behavior and measures of psychosocial functioning. All measures have been used successfully in our prior research in Uganda and have been translated into Luganda, the primary native language used in the study setting. Participants will receive 10,000 Ush (~\$4 USD) for each assessment.

**Longitudinal provider cohort:** The provider cohort will be surveyed at the start of intervention implementation and then at months 6, 12 and 24. The measures will include perceived competency in providing depression care, quality of depression treatment provided, effects of the treatment model on clinic functioning, provider burden and patient flow, and impact of depression treatment on the patient's quality of life.

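### The between-arm comparison of dosing fidelity relies in part on supervisors who know the arm and score charts on which they have advised; score it by one rule from the treatment registry instead

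*Protocol*

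**What the plan says.** The Study Overview names fidelity among the parameters on which the two models are compared, and Section 7.0 treats it as adherence to the care model.

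One of the four data sources in Section 7.0 is "monthly logs summarizing chart abstracted data completed by the supervising psychiatrists". For newly prescribed patients the log holds the "number with correct diagnosis, correct prescribed antidepressant, and correct prescribed dosage". For patients in ongoing treatment it holds the "number correctly assessed for depressive symptoms and side effects; number correctly dosed", plus return for follow-up. Section 6.3 gives this review a central place: "Ongoing supervision and review of cases is our primary mechanism for monitoring the fidelity of the implementation of the treatment models". Each month it covers every patient prescribed in the past month and 10 randomly chosen ongoing charts.

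Section 6.3 also describes what else these psychiatrists do. They mentor providers on site for the first 4-6 weeks. After that, in monthly individual sessions, they discuss new, problematic and nonresponding cases and "the treatment plan for the patient, including side effect management and dose change recommendations". This happens in both arms.

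On the comparator, Section 6.2 says that "the clinical acumen model of depression care relies on the discretion of primary care providers". Section 6.3 says of training and supervision that "the only differences are that the providers in the clinical acumen arm will not be trained to follow the parameters of a structured protocol", and it ties this to the further assessment of patients who screen positive.

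**The concern.** The person who counts a chart as correctly dosed may have advised on that dose a month earlier, and knows which model the clinic runs. For coaching this does no harm. For a comparison between arms, the count mixes what providers did with how the supervisor judges it, and that judgment may differ between an arm with an algorithm and an arm built on clinical judgment. If the rule behind the word correct is not the same in both arms, or is not settled, a finding of equal or of better dosing fidelity cannot be read with confidence.

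**Working it through.** The protocol gives no expected rate, sample size or power for fidelity, so there is no figure to reproduce. The check has three parts.

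**1. How far scorer and adviser overlap.**
- *New prescriptions (drug and starting dose).* Providers present new cases that have arisen since the last session, so the prescription is normally written before the supervisor sees it. Overlap is small, except in the 4-6 weeks of start-up, when supervisors may co-conduct assessments.
- *Ongoing charts (correctly dosed).* A problematic or nonresponding case discussed one month can be among the 10 charts drawn at random the next. Overlap is real but partial, and the protocol gives no figure for its share.
- *Masking.* None is described. Knowledge of arm follows from the role: supervisors work on site with nurses in one arm and with primary care providers in the other.

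**2. Direction of the bias.** Let p be the true share correctly dosed in an arm, and f the share of truly incorrect charts that the scorer passes as correct. The observed share is p + (1 - p) × f. All values below are assumptions.

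| True p, protocolized / acumen | f, protocolized / acumen | Observed shares | True gap | Observed gap |
|---|---|---|---|---|
| 90% / 70% | 0.50 / 0.50 | 95.0% / 85.0% | 20 | 10 |
| 90% / 70% | 0.25 / 0.75 | 92.5% / 92.5% | 20 | 0 |
| 90% / 70% | 0.75 / 0.25 | 97.5% / 77.5% | 20 | 20 |
| 90% / 70% | 0.50 / 0 | 95.0% / 70.0% | 20 | 25 |
| 80% / 60% | 0.25 / 0.75 | 85.0% / 90.0% | 20 | -5 |
| 70% / 70% | 0.75 / 0.25 | 92.5% / 77.5% | 0 | +15 |
| 70% / 70% | 0.25 / 0.75 | 77.5% / 92.5% | 0 | -15 |

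Equal leniency shrinks a gap. Unequal leniency can hide, reverse, enlarge or create one. Nothing in the protocol fixes f in either arm.

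**3. The standard behind the word correct.**
- *Which rules apply in the clinical acumen arm.* The prescribing paragraph of Section 6.1 names the providers of both arms and contains the drug-selection rule. Section 6.3 confines the training difference to further assessment. Both suggest shared drug and dose rules. Against this, Section 6.2 rests diagnosis and treatment on provider discretion, and Section 11.2 leaves monitoring in that arm to the primary care provider as usual care. The visible text does not settle the matter.
- *The algorithm itself.* Section 6.1 gives one imipramine increment as 25 mg; the footnote to Figure 2 gives 50 mg/day. From 75 mg, a one-increment increase ends at 75 + 25 = 100 mg under one passage and 75 + 50 = 125 mg under the other. The same chart would be scored right or wrong depending on the passage used, even in the protocolized arm.

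**The case against.** The strongest reply is that supervision belongs to both models. Section 6.2 includes monthly psychiatrist supervision in the clinical acumen arm, so a dose given on the supervisor's advice is the model as delivered. That stands. Supervised decisions belong in the main analysis, and removing them would select on events after randomization, mainly problematic and nonresponding cases.

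It is also true that the log is not the only source. Section 6.1 already names registry data for tracking fidelity, and Section 7.0 speaks of triangulating sources. But no passage says that the registry, rather than the log, decides the dosing comparison, and the dosing counts are defined only in the log.

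Three stronger readings are tempting and are not supported:
- *That the bias runs toward no difference.* With assumed true rates of 90% and 60% and the same f in both arms, the observed gap is (1 - f) × 30 points: 22.5, 15 and 7.5 at f = 0.25, 0.50 and 0.75. This needs equal f in the two arms, which the protocol does not establish.
- *That the choice of antidepressant is self-scored.* That item is counted only for new prescriptions, which normally precede review.
- *That dosing in the clinical acumen arm is discretionary or has no standard.* Section 6.2 places discretion over whether to evaluate and treat and does not name dosing. Table 1, Figure 2 and the training manual are not visible and may give the rule.

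**Conclusion.** The concern holds in a limited form. The count of correctly dosed ongoing patients is partly self-scored, by raters who know the arm, and it feeds a comparison between arms. The bias has no determined direction. Its size cannot be taken from the protocol: the 15-point shifts above rest on assumed rates and assumed leniency. Two matters of text add to it: the unclear reach of the Section 6.1 drug and dose rules in the clinical acumen arm, and the two imipramine increments.

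The knowledge of arm is inferred from the supervisors' role rather than stated. Importance is moderate. Fidelity appears in the Study Overview but not among the aims in Section 2.0, and neither treatment uptake nor PHQ-9 change uses these logs.

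**What to change.** 1. Reconcile the two imipramine increment passages (Section 6.1 and the Figure 2 footnote). State in Section 6.2 which Section 6.1 drug and dose rules apply to clinical acumen providers.
2. Keep the supervisor log for coaching and as supporting data.
3. Take the between-arm dosing comparison from the Depression Treatment Registry, which at each site already records PHQ-9, side effects, drug and dose per visit. Apply one written rule by program, identically in both arms and without arm labels. Where the algorithm leaves a choice to the provider, as for partial responders, count every permitted option as concordant.
4. Report the result as concordance with the algorithm in both arms, since the clinical acumen arm may not be bound by it.
5. Keep supervised decisions in the main analysis. Any exclusion of supervisor-advised decisions should be a sensitivity analysis only; it would need one extra registry field showing whether the decision came before or after advice.

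The cost is a scoring program on data already abstracted. The downside is that registry entries may be less complete than reviewed charts, possibly more so where monitoring is left to the provider, so missing visits should be reported by arm. The written rule must also say how tolerance is read, because Section 7.0 records the presence of side effects while the algorithm turns on whether they are tolerated.

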## 8.0 MEASURES

### **Quality of depression care measures**

**Depression** is assessed with depression module of the Patient Health Questionnaire. The 9 items are the 9 DSM symptom criteria for Major Depression; a "past 2 weeks" time frame is used and each item is scored from 0 'never' to 3 'every day'. Total score ranges from 0-27; scores 1-4 is min. depression, 5-9 'mild', 10-14 'moderate', 15-19 'moderately severe', and 20+ 'severe'. The first two items (depressed mood and loss of interest) compose the PHQ-2 screen, and a sum score  $\geq 3$  represents a positive screen for depression. The PHQ-2 has high specificity (95%) and sensitivity (85%) for PHQ-9 diagnosed depression in PLHA in SSA, and PHQ-9 has high sensitivity and specificity (both 88%) with MDD by diagnostic interview. The Mini Neuropsychiatric Interview screening modules will be used to rule out Bipolar Disorder and psychosis.

**Response to antidepressant treatment:** full response defined as PHQ-9  $< 5$  and tolerating any side effects.

**Antidepressant side effects** will be assessed with an adapted Antidepressant Side Effect Checklist (ASEC), which enquires about symptom severity of common antidepressant side effects (e.g., dry mouth, nausea, diarrhea) on a scale of 0 'absent' to 3 'severe' and perception of the symptom as a side effect of the antidepressant. It will be used by the DCM in the task-shifting model, as well as the survey assessment.

**Quality of life and functioning** will be assessed with the Medical Outcomes Study HIV Health Survey. A Luganda version has been validated. The MOS-HIV includes subscales of physical function, social and role function, cognitive function, pain, mental health, energy, distress about health, quality of life and overall health.

### **Public health outcomes**

**Work** We will draw on the employment module of the Uganda National Integrated Household Survey to assess work activities (e.g., formal salary, farming, to selling goods) and amount of income and hours worked.

**Sexual risk behavior** will be assessed including frequency of sexual intercourse; number and type (main, casual, commercial) of sex partners, and condom use (at last sex and in general in separate items) over past 6 months, as well as HIV status disclosure from and with reported sex partners.

**ART and antidepressant adherence.** We will ask about number of missed doses over past 7 days, as well as a visual analog scale to measure adherence (0 to 100%) to ART (if applicable) and antidepressants. All patients receive their medication from the clinic pharmacy, so pharmacy refill data will also be used to assess a composite measure of refill rate across ART medications, as well as the antidepressant. **Clinic attendance** will be gauged from chart abstraction and self-report about missed appointments in past 6 months.

## Other measures

**Demographics** will include age, sex, ethnic tribe, position in household, education level, relationship status. **Alcohol use** will be assessed using the 4-item Alcohol Use Disorders Identification Test (AUDIT).

**HIV characteristics:** HIV test date, WHO disease stage, CD4, and medications used will be chart abstracted.

**Treatment-related attitudes and beliefs.** Measures of perceived efficacy of treatment (2 items), perceived social support for treatment (2 items), and adherence self-efficacy (1 item), adapted from ACTG measures.

**General self-efficacy and expected outcomes.** We developed 5-item Likert-scale measures of self-efficacy and expected outcomes for tasks such as work, condom use, caregiving, and forming social relationships.

**Use of mental health services** (e.g., psychosocial counseling) over past 6 months will be assessed.

**Process Measures:** We will collect clinic structural data and implementation process measures in order to identify lessons learned for scaling up depression treatment and inform the generalizability of our findings.

**Structural measures:** Site visits and interviews with clinic administrators will be conducted prior to the implementation of the treatment models and then every 6 months for 24 months to assess: staff composition (number and type of providers), staff turnover, number of patients in care, presence of ancillary services (e.g., nutrition, school fees support, income generating activities), change in donor/funding levels, availability of ART.

**Provider experience:** We will develop Likert rating scales for DCMs and physicians to complete on a quarterly basis from the start of treatment implementation to assess their perception of: self-efficacy in providing depression treatment; quality of depression treatment provided; effects of the treatment model on clinic functioning, provider burden and patient flow; and impact of depression treatment on the patient's quality of life.

**Patient experience:** Patients enrolled in the study will be asked to rate their satisfaction with the treatment effects on quality of life and perceived competency of providers to manage treatment at each follow-up visit.

**Patient attendance:** Patient attendance at antidepressant monitoring visits will be recorded.

## 9.0 STATISTICAL ANALYSES

**9.1 Power analysis for primary aims.** With 10 clusters, this study is powered to detect medium to large effect sizes; nonetheless, the results will be among the first of their kind, hence informative for subsequent analysis and policy. We calculated detectable differences for different intracluster correlation coefficient (ICC) values. Data from developing countries indicate low correlations of health outcome variables within primary care settings (improving power), including .03 for depression in a collaborative care trial in India, and .011 for maternal/perinatal health outcomes in 8 Latin American countries. ICC tends to be higher for process related measures (which would include the focus of Aim 1a): median=.16 for the same 8 country study.

**Aim 1a (treatment uptake):** With 150 patients per site and assuming 30% antidepressant uptake in the standard model and ICC=.16, we will be able to detect an increase of 28% in uptake rates between the task-shifting and standard clinics ( $\alpha = .05$ , 80% power; one sided test). For ICC=.25 the increase is 34%. Given the systematic procedural difference in the two arms, we expect the actual difference may exceed these amounts.

**Aim 1b (depression change):** For measuring change in PHQ-9 in an intention to treat (ITT) analysis using the whole sample, with ICC =.025, s.d. =3.9 (from our current study), and 10% attrition, we'll have power to detect a 1.26 difference on the PHQ-9 ( $\alpha = .05$ , 80% power; 2-sided

test); for ICC=.01 and .05, detectable differences are .92 and 1.71. For analysis of those receiving antidepressants, we estimate 30% (n=45) of the standard arm patients will be treated (a larger share is expected in the task-shifting arm, which will improve power). With ICCs =.01, .025, and .05 (s.d. = 3.0), and 10% attrition, we will be able to detect changes of 1.00, 1.20, and 1.46 in the PHQ-9. These correspond to medium effect sizes (Cohen's *d*) of 0.33, 0.40 and 0.49.

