## STUDY OVERVIEW

**DESIGN:** A comparative trial that compares two implementation models for integrating antidepressant treatment into HIV care within 10 health care facilities in Uganda. Using a cluster randomization, 5 clinics are assigned to implement a protocolized model, and 5 others rely on the clinical acumen of trained providers. To evaluate the models, data will be collected from documentation mechanisms integrated into routine care, and from random samples of 100-150 patients enrolled at each site that screen positive for possible depression and are followed for 12 months. A cohort of providers will also be enrolled at each site and followed over 24 months. We will compare the two models on uptake of antidepressant treatment, and change in depression (treatment response), as well as other quality of care outcomes.

**STUDY SITES:** Of the 10 healthcare facilities participating in the study, eight are run by the Ministry of Health and two are private, faith-based, not-for-profit healthcare facilities; two are district hospitals and the others are designated as health centre III or IV facilities by the Uganda Ministry of Health, and are located in the districts of Mpigi, Mityana, Luweero, and Wakiso.

**SAMPLE SIZE:** 10 clusters (clinics), with 100-150 patients at each clinic.

**POPULATION:** Over the course of 12 months at each site, research coordinators (Masters level graduates with social science training) will recruit random samples of 100-150 patients who the triage personnel screen as positive for potential depression (PHQ-2 > 2), who are confirmed to be positive in the research coordinator's own PHQ-2 administration, and who are determined to be medically stable.

**STRATIFICATION:** To ensure the two study arms are balanced on size of clientele (small clinics serve 300-1000 clients, while larger clinics serve 1500-3000 clients), which could influence depression care processes, randomization will be conducted within pairs of clinics that were matched on this variable.

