## 3.0 STUDY DESIGN

INDEPTH-Uganda is a comparative trial that compares two active task-shifting implementation models for integrating antidepressant treatment into HIV care within 10 health care facilities in Uganda. Using a cluster randomization, 5 clinics are assigned to implement a protocolized model, and 5 others rely on the clinical acumen of trained providers. To evaluate the models, data will be collected from documentation mechanisms integrated into routine care, and from random samples of 100-150 patients enrolled at each site that screen positive for possible depression and are followed for 12 months. We will compare the two models on uptake of antidepressant treatment, and change in depression (treatment response), as well as other quality of care outcomes.

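### The detectable uptake differences printed for Aim 1a (28 and 34 points) do not follow from the 10 clinics randomised; 5 clinics per arm give about 30 and 37, or 33 and 40 with 8 degrees of freedom

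*Protocol*

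**What the plan says.** The Study Overview gives the sample size as "10 clusters (clinics), with 100-150 patients at each clinic". Section 3.0 fixes the split: "5 clinics are assigned to implement a protocolized model, and 5 others rely on the clinical acumen of trained providers". Section 9.1 opens on the same footing: "With 10 clusters, this study is powered to detect medium to large effect sizes".

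The Aim 1a paragraph of section 9.1 then sets its inputs, "With 150 patients per site and assuming 30% antidepressant uptake in the standard model and ICC=.16", and its error rates, alpha .05 with "80% power; one sided test". From these it concludes that "we will be able to detect an increase of 28% in uptake rates between the task-shifting and standard clinics". It adds a second case, "For ICC=.25 the increase is 34" (per cent).

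Section 9.2 says that, for most outcomes, clinic means or proportions will be compared first by t-test, weighted by cluster size where clinics contribute unequal numbers. Individual-level regression follows, with significance examined over a range of plausible ICCs.

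**The concern.** Every input to the Aim 1a figures is printed, so they can be checked directly. When they are put through the usual design-effect formula with 5 clinics per arm, both printed differences come out too small. The trial would then need a larger true difference than stated to reach 80% power.

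Uptake is the first quality-of-care indicator under the first primary aim, and this paragraph is its only statement of power. If the trial finds no significant difference in uptake, readers will judge that result against a 20% chance of having missed 28 points. On the plan's own inputs that chance is 26% to 33%.

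**Working it through.** **Inputs (section 9.1 unless noted).** Patients per clinic m = 150. Standard-arm uptake p0 = .30. ICC = .16 or .25. One-sided alpha .05 and 80% power, so z = 1.645 + 0.842 = 2.486. Clinics per arm k = 5 (section 3.0). The printed 28% and 34% are read as percentage points. A relative reading (28% of 30% = 8.4 points) would be much further out of reach.

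**Formula.** Design effect DE = 1 + (m − 1) × ICC. Effective number per arm n = k × m / DE. The detectable difference d solves d = 2.486 × √{[.30 × .70 + (.30 + d)(.70 − d)] / n}. This is the unpooled normal approximation.

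**Attempt to reproduce with k = 5.**
- ICC .16: DE = 1 + 149 × .16 = 24.84; n = 750 / 24.84 = 30.2; d = .303.
- ICC .25: DE = 1 + 149 × .25 = 38.25; n = 750 / 38.25 = 19.6; d = .369.

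The printed .28 and .34 are not reproduced. The choice of formula does not close the gap:

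| Method, 5 clinics per arm, one-sided | ICC .16 | ICC .25 |
|---|---|---|
| Printed in section 9.1 | 28 | 34 |
| Control-arm variance only (most lenient) | 29.3 | 36.4 |
| Unpooled z | 30.3 | 36.9 |
| Pooled variance under the null | 31.3 | 38.7 |
| Arcsine | 31.3 | 38.7 |
| Noncentral t, 8 df | 33.0 | 39.9 |

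For the last row, df = 2k − 2 = 8, as for an unpaired comparison of 5 against 5 clinic proportions. With 100 patients per clinic, the lower end of the design range, unpooled z gives 30.6 and 37.0, so cluster size is not the explanation.

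**Power at the printed differences, k = 5.**
- 28 points, ICC .16: SE = √[(.30 × .70 + .58 × .42) / 30.2] = .1226; .28 / .1226 = 2.284; Φ(2.284 − 1.645) = 74%. Noncentral t on 8 df: 67%.
- 34 points, ICC .25: SE = √[(.30 × .70 + .64 × .36) / 19.6] = .1499; .34 / .1499 = 2.269; Φ(2.269 − 1.645) = 73%. Noncentral t on 8 df: 67%.

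A beta-binomial simulation of the one-sided clinic-level t-test gives about 65% and 64%. The most lenient formula, control-arm variance only, gives 77% and 75%.

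**What does reproduce the figures.** With k = 6, n = 900 / 24.84 = 36.2 and 900 / 38.25 = 23.5. Unpooled z then gives d = 27.8 and 34.0 points, with power of 80.4% and 80.0% at 28 and 34. Seven clinics per arm also round to the printed pair if t quantiles on 12 df replace z (27.5 and 33.7), or if one cluster per arm is deducted as a small-sample correction (27.8 and 34.0).

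**The case against.** **The gap is small next to the other uncertainties.** Like for like, it is 2.3 points at ICC .16 (30.3 against 28) and 2.9 at ICC .25 (36.9 against 34). Moving the ICC from .16 to .25 shifts the printed figure by 6 points, and the .16 is borrowed from process measures in another study. Section 9.1 already concedes that only medium to large effects are detectable, and it expects a true difference that could be larger than the printed ones. All of this stands, and it keeps the size of the point moderate. It does not make the printed figures right: they are offered as the result of stated inputs, and they are not that result.

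**Eight degrees of freedom are not fixed by the plan.** Section 9.2 treats individual-level regression as the main approach. Clinics are randomised within matched pairs, so a paired analysis would have 4 df. This also stands, and it is why the error is established on the normal approximation alone. The t figures are given because a clinic-level t-test is the first analysis that section 9.2 names for most outcomes.

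**Three stronger readings are tempting, and the documents do not carry them.**
- A reader might infer that the calculation was done for 12 clinics. The protocol never mentions 12, and 14 clinics under other conventions round to the same figures.
- A reader might infer that Aim 1b was powered on a different design. The Aim 1b figures do not settle this. The protocol prints .92, 1.26 and 1.71 (whole sample) and 1.00, 1.20 and 1.46 (treated patients). Ten clinics with z give .91, 1.24, 1.65 and .99, 1.18, 1.44. Twelve clinics with t quantiles give .92, 1.26, 1.67 and 1.00, 1.19, 1.46, which fit at least as well.
- A reader might count the one-sided test as part of the error, because Aim 1b is two-sided, and demand the two-sided figures (about 38 and 45 points with 8 df). But the one-sided basis is openly stated, agrees with the directional hypothesis in section 2.0, and appears only in the power paragraph. The uptake analysis in section 9.2 specifies no one-sided test. Preferring two-sided is a choice of method, not a correction of the arithmetic.

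**Conclusion.** The Aim 1a figures are wrong as written. With 10 clinics and the stated inputs, the detectable increases are about 30 points (ICC .16) and 37 points (ICC .25) by unpooled z, with ranges of 29–31 and 36–39 across the normal approximations tabulated. With a clinic-level t-test on 8 df they are about 33 and 40. At the printed 28 and 34 points, power is about 74% and 73% (z), or 67% at both (t), against the stated 80%.

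This assumes equal clinics of 150, one common ICC in both arms, the standard design effect and no gain from pair matching, which the paragraph does not claim. That a different cluster count was used is a plausible explanation, not an established fact. The design itself is not called into question; the power statement is.

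**What to change.** Recompute the Aim 1a paragraph of section 9.1 for 5 clinics per arm on its stated one-sided basis, and name the formula. Then do one of the following:

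- print the corrected detectable differences: about 30 and 37 points by normal approximation or, preferably, about 33 and 40 points with 8 df;
- keep 28 and 34 points and print the power actually available for them: about 74% and 73%, or 67% for both with 8 df.

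At the same time, check that the Aim 1b figures were computed for 10 clinics, and state the cluster count and reference distribution used for both aims. A two-sided version for Aim 1a could be added, but correcting this error does not require it.

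The cost is one rewritten paragraph and a less favourable headline figure. No clinics, patients or analyses change.
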